## **VII. Cognitive, Mood, Well-being, and Physical Activity assessment questionnaire/ tests**

Participants will complete a neuropsychological assessment at each post-stroke time-point (Baseline, 4 months, 1 year). Seven cognitive domains (global cognitive ability, attention, processing speed, visuospatial ability, memory, language, and executive function) will be assessed using a neuropsychological battery developed from CANVAS that takes approximately 90 minutes [3]. The battery will include three computerised tests from the CogState Battery as well as the following standard paper-and-pencil tests:

| Cognitive Domain         | Cognitive task                                                                                                                                                                                                                                                                                                                                                                                     |
|--------------------------|----------------------------------------------------------------------------------------------------------------------------------------------------------------------------------------------------------------------------------------------------------------------------------------------------------------------------------------------------------------------------------------------------|
| Global Cognitive Ability | 
 
- Montreal Cognitive Assessment (MoCA) (original version at baseline; alternate versions at 4 and 12 months post-stroke)
 
- Alzheimer's Disease Assessment Scale-Cognitive Subscale (ADAS-Cog) (only administered at Baseline and 12 months post-stroke as no alternate versions are available, to counteract possible practice effects)
 
 |
| Attention                | 
 
- Digit Span Task from the Weschler Adult Intelligence Scale-Fourth Edition (WAIS-IV)
 
- Trail-Making Test (TMT)
 
- Identification Task (Computerised CogState battery)
 
- One Back Task (Computerised CogState battery)
 
                                                                                                 |
| Processing Speed         | 
 
- Digit-Symbol Coding Task from the WAIS-IV
 
- Detection Task (Computerised CogState battery)
 
                                                                                                                                                                                                                                            |
| Visuospatial Ability     | 
 
- Rey Complex Figure (RCF) - Copy
 
- Cancellation Task from the WAIS-IV
 
                                                                                                                                                                                                                                                                  |
| Memory                   | 
 
- Hopkin's Verbal Learning Test – Revised (HVLt-R)
 
- Rey Complex Figure (RCF) - Recall
 
                                                                                                                                                                                                                                                  |
| Language                 | 
 
- Verbal Fluency Task (VFT)
 
- Boston Naming Test (BNT)
 
                                                                                                                                                                                                                                                                                  |
| Executive Function       | 
 
- Clock Drawing Test (CDT)
 
                                                                                                                                                                                                                                                                                                                       |

All of these tasks have been designed for serial testing and are not subject to practice effects. In the case of the HVLIT-R and Cancellation Task, alternate forms are available to use on repeat administrations. Performance on individual cognitive tests will be standardised using established norms, and domain scores will be calculated by averaging the standardised scores from each contributing test (e.g., digit span and digit symbol for the attention domain). In addition, the National Adult Reading Task (NART) will be used to estimate full-scale IQ; the Modified Rankin Scale (mRS) will be used to assess ability to function daily; the National Institute of Health Stroke Scale (NIHSS) will be used to assess neurological function; and the Fugl-Meyer Upper Limb Assessment will be used to provide a more detailed assessment of motor function, specifically for the upper limb and hand. The NART will be administered at one time-point, the mRS, Fugl-Meyer Assessment, and NIHSS will be administered at every time-point.

Assessment of mood will be completed using the Patient Health Questionnaire (PHQ-9) and the Generalised Anxiety Disorder 7-item scale (GAD-7). These questionnaires are based on criteria for the diagnosis of generalised anxiety and depression, as outlined in the Diagnostic and Statistical Manual-Fourth Edition (DSM-IV, no updated tests are yet available according to updated DSM-V criteria).

'Quality of life' will be quantified using the Assessment of Quality of Life (AQOL). Self-perceptions of fatigue will be recorded using the Fatigue Assessment Scale (FAS). Both of these scales have been developed for research projects and have been extensively used by the Investigators.

Subjective memory loss/improvement will be assessed at each time-point with the Memory Assessment Clinic-Questionnaire (MAC-Q), a validated and widely used 6-item questionnaire to measure self-report memory complaints over time.

Self-report physical activity will be assessed via the Physical Activity Scale for the Elderly (PASE), a validated and widely used questionnaire to track typical physical activity levels in an older adult population over a one-week period. We will administer the PASE in person at the 2-month, 4-month, and 12-month time-points, and over the telephone at 6, 8, and 10 months post-stroke. This will be administered to gauge activity levels outside of the intervention throughout the course of the study.

At the completion of the study, participants who request information regarding their cognitive test progress will be provided with a letter indicating whether they are performing at, below, or above cognitive norms standardised for age. This letter will also be accompanied by the flyer "*What Can I Do to Improve My Body and Brain Health?*", which provides participants with information for how to improve their body and brain health, and encourages them to seek further referral advice from their local doctor should they have any concerns about their health, particularly regarding cognition.

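### The Global Cognitive Ability score averages two tests at baseline and 12 months but rests on MoCA alone at 4 months, so change to or from the 4-month visit in that domain is not like for like

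*Protocol*

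**What the plan says.** All statements are in Protocol section 5.d.VII.

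- Schedule: "Participants will complete a neuropsychological assessment at each post-stroke time-point (Baseline, 4 months, 1 year").
- Scoring, once each test has been normed, follows this rule: "domain scores will be calculated by averaging the standardised scores from each contributing test (e.g., digit span and digit symbol for the attention domain").
- Global Cognitive Ability in the battery table: MoCA, with "original version at baseline; alternate versions at 4 and 12 months post-stroke", and ADAS-Cog, "only administered at Baseline and 12 months post-stroke as no alternate versions are available, to counteract possible practice effects".
- Attention in the table: Digit Span, Trail-Making, Identification and One Back. The "Digit-Symbol Coding Task from the WAIS-IV" sits under Processing Speed. The scoring sentence instead gives "digit span and digit symbol for the attention domain".
- Practice effects, in the text after the table: "All of these tasks have been designed for serial testing and are not subject to practice effects".

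On the role of cognition, the Study Synopsis (Primary Objectives) uses concurrent neuropsychological testing to see whether the clinical picture agrees with brain volume. Section 4.c lists no cognitive outcome. Section 8.c(iii) names cognitive function among the metrics for analyses it calls exploratory.

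**The concern.** A change score is interpretable only if the same thing is measured at both ends. Under the stated rule the global composite loses one of its two components at 4 months and regains it at 12 months. The 4-month visit is the post-intervention visit and the time of the primary brain-volume outcome, so it is the visit at which a reader will most want to see cognitive change. A participant whose cognition is stable would show an apparent gain or loss at 4 months and the reverse by 12 months, which is a false kink in a three-visit trajectory.

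The attention conflict is a different kind of defect. Two analysts following the same section could build two different attention scores, and possibly two processing-speed scores. The conflict over practice effects is one of wording: the table withholds a test on grounds that the later text says do not apply.

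**Working it through.** The plan gives no figure of its own on this point, so there is none to reproduce.

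**Step 1. Membership by visit, from the battery table.**

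| Domain | Baseline | 4 months | 12 months |
|---|---|---|---|
| Global | MoCA + ADAS-Cog | MoCA | MoCA + ADAS-Cog |
| Other six domains | all listed tests | all listed tests | all listed tests |

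Only the global domain has membership that depends on the visit.

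**Step 2. Shift with no true change.** Let M and A be the norm-standardised MoCA and ADAS-Cog scores, both oriented so that higher is better.

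- Baseline to 4 months: M − (M + A)/2 = (M − A)/2.
- 4 to 12 months: (M + A)/2 − M = −(M − A)/2.
- Baseline to 12 months: (M + A)/2 − (M + A)/2 = 0.

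The protocol does not give the gap M − A, so it is assumed:

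| Assumed gap (SD) | Apparent change to 4 months (SD) |
|---|---|
| 0 | 0 |
| 0.25 | 0.125 |
| 0.5 | 0.25 |
| 1.0 | 0.5 |

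**Step 3. Variance of change.** Assume unit variances, a same-visit MoCA/ADAS-Cog correlation ρ, a MoCA retest correlation r, and a correlation ρr between baseline ADAS-Cog and 4-month MoCA.

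- MoCA at both visits: 2 − 2r.
- Mismatched composite: 1 + (2 + 2ρ)/4 − (r + ρr).
- Difference: (1 − ρ)(r − 0.5), which is positive whenever r exceeds 0.5 and ρ is below 1.

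Example with ρ = 0.6 and r = 0.8: 1 + 0.80 − (0.80 + 0.48) = 0.52, against 2 − 1.6 = 0.40. The SDs are 0.72 and 0.63.

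| r | SD, MoCA only | SD, mismatched, ρ = 0.8 | ρ = 0.6 | ρ = 0.4 |
|---|---|---|---|---|
| 0.7 | 0.775 | 0.800 | 0.825 | 0.849 |
| 0.8 | 0.632 | 0.678 | 0.721 | 0.762 |
| 0.9 | 0.447 | 0.529 | 0.600 | 0.663 |

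The mismatched score is noisier in every row. The penalty is small when the two tests agree closely and retest reliability is modest, and larger in the opposite case.

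**Step 4. Attention.** The table gives four tests and the example gives two; only Digit Span is in both. With a common inter-test correlation ρ, the covariance of the two composites is (1 + 7ρ)/8 and their variances are (1 + 3ρ)/4 and (1 + ρ)/2. For assumed ρ = 0.3, 0.5 and 0.7 their correlation is 0.70, 0.82 and 0.91. They are related but not interchangeable. None of these tests is tied to particular visits, so either definition is the same at baseline, 4 and 12 months.

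**The case against.** The strongest reply is that no analysis stated in the protocol is damaged. The ANCOVA in section 8.c(i) is for brain volume; no model for cognitive change to 4 months is written down; cognition is not in the outcome list in section 4.c. Agreement with brain volume could be examined from 4-month scores alone. How a composite treats a test deliberately left off a visit is the kind of detail that a statistical analysis plan, not seen here, could settle, and the attention wording is offered only as an example.

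Much of this stands and limits the weight of the point. It does not remove it. The protocol does not stay silent on scoring: it states a rule, and that rule combined with the stated schedule gives a score whose content changes. The attention example names a test that the table assigns elsewhere, so calling it an example does not reconcile the two.

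A reader might infer more than the documents support:

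- That the attention conflict also makes change between visits compare different composites. It does not (step 4).
- That the randomised comparison is biased. The shift depends on the baseline MoCA/ADAS-Cog gap, which is expected to be the same in both arms.
- That the correlation of cognition with atrophy is wrong. A common shift leaves a correlation unchanged, and individual differences between the two tests mainly add noise.
- That all cognitive change is affected. It is one domain of seven, and its change from baseline to 12 months is like for like.

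**Conclusion.** The point holds for one domain and for comparisons that involve the 4-month visit. Under the stated rule, change in Global Cognitive Ability to or from 4 months carries a shift of half the MoCA/ADAS-Cog difference. That it exists is algebra; its size, 0.125 to 0.5 SD, rests on assumed gaps of 0.25 to 1.0 SD and would be zero if the two normed scores agreed. The SD of change is 0.53 to 0.85 against 0.45 to 0.77 for MoCA alone, for assumed correlations ρ of 0.4 to 0.8 and r of 0.7 to 0.9. The harm is to within-arm and individual change and to precision, in an exploratory metric.

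The inconsistent attention definition is a separate and real contradiction that leaves an analyst's choice open. The conflict over practice effects is one of wording; no further analytic consequence follows from it.

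**What to change.** In Protocol section 5.d.VII:

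1. State that any global-cognition analysis involving the 4-month visit uses MoCA alone at every visit it includes, and that ADAS-Cog, alone or averaged with MoCA, is used only for change from baseline to 12 months. The two-test composite need not be given up for that longer interval.
2. Replace the attention example with tests that the table lists under Attention, leaving Digit-Symbol Coding under Processing Speed.
3. Limit the sentence on practice effects so that it agrees with the reason given for leaving ADAS-Cog out at 4 months.

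The cost is wording only; no test or visit changes. The small downside is that the 4-month global score rests on one test, which the present schedule already implies. The change should be made before the data are unblinded, so that the choice of composite cannot be informed by results.

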## **VIII. Fitness test of aerobic capacity – VO2 peak graded exercise test (GXT)**

Aerobic capacity will be repeatedly assessed at each study visit via a submaximal, incremental exercise test. At the initial Baseline visit, information from the GXT will also be used to create each participant's graduated exercise programme.

All participants will undergo a  $VO_{2peak}$  graded exercise stress test to determine exercise capacity using a metabolic cart (the Oxycon mobile™, CareFusion). A submaximal GXT will be conducted at each of the three study visits to monitor the change in aerobic capacity. The GXT will take place at the Florey, Melbourne Brain Centre, Austin campus, or in the AIMSS facility at Western Health, under the supervision of a trained exercise professional. This person will not be involved with the exercise training as they are not blinded to participant status.

The following parameters will be recorded during the test:  $VO_{2peak}$  (volume oxygen uptake in ml/kg/min), Heart Rate (HR), Heart Rate Reserve (HRR, subtracting resting heart rate from the maximum heart rate measured during an exercise test), Oxygen Saturation, and Respiratory Rate (RR, number of breaths per minute). These parameters will enable us to derive  $VO_{2peak}$  as an estimate of aerobic exercise capacity. Blood pressure and ECG recordings will be monitored as markers of participant well-being.

A total body recumbent stepper will be used to perform the GXT, as outlined by Billinger [32]. This submaximal GXT protocol has been shown to be a valid measurement of  $VO_{2peak}$  [35], and prescribing cardiorespiratory exercise based on  $VO_{2peak}$  values is safe in a subacute stroke population with mild to severe post-stroke deficits [36].

Participants will be asked to maintain a step rate of 80 steps per minute on a recumbent stepper. The test will start at a power output of 15 watts and will be increased every 2 minutes by an amount that is predefined in the protocol (see Box 1, based on Billinger 2008). The amount will increase until completion or until volitional fatigue, or 85% of age predicted heart rate was achieved ( $0.85[220 - \text{age}]$ ). HR will be recorded every 10 seconds at the end of the second and third minute. If the change in HR between the second and the third minute is less than 5 bpm then the resistance will be moved to the next stage. If it is over 5 bpm an additional minute will be performed at the same stage to make sure steady state will be reached.  $VO_{2peak}$  will be determined by imputing HR and workload into the following equation  $VO_{2peak} \text{ (ml.kg.min)} = 125.707 + (-0.476)(\text{age}) + (7.686)(\text{sex } [0 = \text{female}; 1 = \text{male}]) + (-0.451)(\text{weight in Kg}) + (0.179)(\text{Watts end\_submax}) + (-0.415)(\text{HREnd\_submax})$ .

| Stage  | Resistance (W) | Stepping cadence
(steps x min) | Duration (min) |
|--------|----------------|-----------------------------------|----------------|
| Load 1 | 25             | 80                                | 2              |
| Load 2 | 40             | 80                                | 2              |
| Load 3 | 55             | 80                                | 2              |
| Load 4 | 70             | 80                                | 2              |
| Load 5 | 85             | 80                                | 2              |
| Load 6 | 100            | 80                                | 2              |
| Load 7 | 115            | 80                                | 2              |

|        |     |    |   |
|--------|-----|----|---|
| Load 8 | 130 | 80 | 2 |
|--------|-----|----|---|

*Based on exercise protocol described in Billinger et al. [35].*

The GXT will be stopped using the safety criteria of exercise testing according to the American College of Sports Medicine (ACSM) exercise testing and prescription guidelines [37].

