### ***Cardiovascular events or respiratory events as a result of physical exercise***

Although rare, two common cardiac risks include myocardial ischemia and different forms of arrhythmias. It is estimated that for adults without existing heart disease, the risk of a cardiac event or complication ranges between 1 in 400,000–800,000 hours of exercise. For patients with existing heart disease, an event can occur on average of once in 62,000 hours [43]. The exercise tests and training also involve a risk of vasovagal episodes.

To mitigate the risk of a vasovagal episode or any other significant adverse cardiac event, all participants must be cleared by a consulting physician before commencing the exercise test and exercise training intervention. The exercise testing and training will be in accordance with current guidelines from the ACSM Exercise Testing and Prescription (ACSM, 2013). [name] (Associate Investigator) is experienced in conducting exercise tests and prescribing exercise and will be responsible for training staff involved in the exercise component of the study.

This study is employing a submaximal, graded exercise test, and the exercise intervention includes CRF training at 50 to 75% of the participant's maximal aerobic capacity. It is not anticipated that the participants will be exercising at an intensity that is likely to induce significant adverse events.

Irrespective, the participant will be closely monitored at all times during the exercise test and during the exercise intervention. Participants will be required to nominate somebody the research team can contact in case of emergency during the exercise intervention. This person may also be involved as a study partner and need to attend each of the exercise intervention sessions if the Exercise Professional deems it necessary. All investigators involved in the exercise testing are required to maintain current first aid qualifications.

Participants will be educated about the procedure to follow should any concerning cardiovascular signs or respiratory signs occur off-site (i.e., not at the Austin Health campus, Eastern Health campus, Western Health campus, or The Alfred Centre ) whilst enrolled in the study. Participants will be provided with a 'Participant Adverse Event Notification Form' to document events and notify Investigators.

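### The printed VO2peak equation gives near-zero or negative values for heavier women who reach the heart-rate limit on the lowest stages, and the protocol does not settle whether the equation or the metabolic cart supplies the analysed value

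*Protocol*

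**What the plan says.** Protocol section 5.d.VIII describes a submaximal graded test at all three visits. It has every participant undergo a VO2peak "exercise stress test to determine exercise capacity using a metabolic cart", lists VO2peak in ml/kg/min among the recorded parameters, and says these parameters allow VO2peak to be derived as an estimate. It then says VO2peak "will be determined by imputing HR and workload into the following equation". The test runs until completion, volitional fatigue, "or 85% of age predicted heart rate was achieved", with the limit written as 0.85(220 - age). The table of loads starts at 25 W and rises by 15 W per stage; the text gives a start of 15 W. No valid range for the equation is stated, nor a rule for a result that cannot be right.

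Aerobic capacity is a secondary outcome measure in the synopsis, a correlate of brain volume in secondary hypothesis iii (section 4.a), and a metric in the exploratory regressions of section 8.c(iii), where it is labelled VO2max. The baseline test also informs the exercise programme (section 5.b, Exercise groups and programmes, and section 5.d.VIII). Section 7.a says the intervention "includes CRF training at 50 to 75" per cent of maximal aerobic capacity.

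**The concern.** A linear equation with a weight coefficient of -0.451 per kg and no floor will leave the possible range at some body weight. The question is whether that weight lies within the population the protocol admits, at a stopping point the protocol itself prescribes. It does: the eligibility criteria (synopsis and sections 6.b and 6.c) set no upper limit on age or weight, and reaching the heart-rate limit is a listed way for the test to end.

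A capacity of zero or below is not a measurement. In a regression that relates the level of aerobic capacity to brain volume, such a value sits at the extreme of the predictor and can have undue influence in a sample of 120 or fewer. A percentage of such a value also has no meaning, so the passages that link the test to exercise intensity say nothing usable for that participant.

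The remedy may already be in the data, because the cart records gas exchange in the same test. The protocol does not say how the cart reading and the equation relate.

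**Working it through.** **Inputs, all from section 5.d.VIII.** Intercept 125.707; age -0.476 per year; male +7.686 (female 0); weight -0.451 per kg; final watts +0.179; final heart rate -0.415 per bpm. Heart-rate limit 0.85(220 - age). Loads 25, 40, 55 W and upward. The protocol prints no worked VO2peak, so there is no stated figure to reproduce.

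**Step 1. Put the limit into the equation.** 0.85(220 - age) = 187 - 0.85 age. Then 0.415 x 187 = 77.605 and 0.415 x 0.85 = 0.35275. The intercept becomes 125.707 - 77.605 = 48.102, and the age coefficient becomes -0.476 + 0.35275 = -0.12325. So, for a test that ends at the limit:

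VO2peak = 48.102 - 0.12325 age + 7.686 male - 0.451 kg + 0.179 W

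**Step 2. One case in full.** Woman of 75, 25 W: 48.102 - 9.244 + 4.475 = 43.333. At 90 kg: 43.333 - 40.590 = 2.74. At 100 kg: 43.333 - 45.100 = -1.77.

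**Step 3. Other women at the limit (ml/kg/min).**

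| Age, load | 70 kg | 80 kg | 90 kg | 100 kg | 110 kg |
|---|---|---|---|---|---|
| 75, 25 W | 11.8 | 7.3 | 2.7 | -1.8 | -6.3 |
| 70, 25 W | 12.4 | 7.9 | 3.4 | -1.2 | -5.7 |
| 70, 40 W | 15.1 | 10.6 | 6.0 | 1.5 | -3.0 |
| 70, 55 W | 17.7 | 13.2 | 8.7 | 4.2 | -0.3 |

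**Step 4. Weight at which the result is zero.** kg = (48.102 - 0.12325 age + 7.686 male + 0.179 W) / 0.451.

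- Women, 25 W: age 85, 42.101 / 0.451 = 93.3 kg; age 45, 47.031 / 0.451 = 104.3 kg.
- Women, 40 W: each rises by 0.179 x 15 / 0.451 = 5.95 kg, giving 99.3 and 110.2 kg.
- Men: each rises by 7.686 / 0.451 = 17.0 kg; for a man of 70 at 25 W, 114.5 kg.
- At the 15 W start given in the text, a woman of 75 reaches zero at 41.543 / 0.451 = 92.1 kg.

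**Step 5. How many (assumptions, not protocol figures).** Take women's age as mean 66, SD 12, and weight as mean 72-78 kg, SD 15-17, normal and independent. At 25 W the mean prediction is 52.577 - 8.135 - 0.451 x 72 = 11.97, with SD sqrt[(0.12325 x 12)^2 + (0.451 x 15)^2] = 6.93, so z = -1.73 and about 4% fall at or below zero. With 78 kg and SD 17, the figures are 9.27 / 7.81, z = -1.19, about 12%. At 40 W, adding 2.685 to the means gives about 2% and 6%.

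These rates apply only to women who end at that load and at the limit. If 35-45% of 120 are women (42-54), 5-15% of them end at 25 W and 10-25% at 40 W, all at the limit, the expected number per visit runs from 42(0.05 x 0.04 + 0.10 x 0.02) = 0.2 to 54(0.15 x 0.12 + 0.25 x 0.06) = 1.8, before attrition.

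**Step 6. Change within a person.** The intercept and sex term cancel between visits. If weight is stable, so does the weight term, and age moves the result by less than 0.5 over the ten months of follow-up. What remains is 0.179 times the change in watts minus 0.415 times the change in heart rate. An impossible level does not by itself distort the change.

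**The case against.** The strongest reply is that any linear prediction fails at extreme inputs, and that range checks belong in an analysis or data-management plan that is not shown here. This stands in part: a bare absence of a range check would be no finding. But the protocol fixes the equation, the stopping heart rate and the loads, and together they yield impossible values for eligible people. That is a badly fixed derivation.

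The heart-rate limit is also the worst case for a given load. Each beat below it adds 0.415, so the woman of 75 at 100 kg and 25 W turns positive about 4.3 bpm under the limit (1.77 / 0.415) and gets 5.8 at 105 bpm. Physician clearance (section 7.a) and the stopping criteria in section 5.d.VIII may remove some of the least fit. These points stand and limit the number affected, but reaching the limit is not itself an exclusion.

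Three stronger readings are tempting and not supported.

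- A reader might infer that impossible values will be common. The percentages in step 5 are conditional, and the protocol gives no weights, sex split or stopping stages.
- A reader might infer that the treatment comparison of fitness gains spurious variance. Step 6 shows that the offending terms largely cancel in within-person change, and no leverage was computed for any analysis.
- A reader might infer that the cart data go unused. Section 5.d.VIII says capacity is determined with the cart and lists VO2peak as recorded, so the source is ambiguous. If the cart value is the one analysed, the problem does not reach the outcome.

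On prescription, section 5.b also adjusts programmes on heart rate and perceived exertion, so the passages do not flatly contradict the equation. They leave open what is used when it gives no usable value.

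**Conclusion.** The point holds with limited reach. At the protocol's own heart-rate limit, the printed equation gives near-zero or negative VO2peak for women of roughly 90 kg and above on the lowest stages, with zero reached at about 93-104 kg (25 W) and 99-110 kg (40 W) for ages 85 to 45. This is exact arithmetic on printed figures. Lighter women, later stages and most men are unaffected.

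Under the stated assumptions, about 0.2 to 1.8 women per visit would have a value of zero or below; small positive values that are still too low would add to this by an amount that cannot be computed. The exposure is mainly in analyses of the level of aerobic capacity (secondary hypothesis iii and section 8.c(iii)). The primary brain-volume analysis is untouched. Whether the coefficients match the cited source cannot be checked from the protocol. The ambiguity between cart and equation needs settling whatever the number affected.

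**What to change.** In section 5.d.VIII:

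1. State which VO2peak is analysed, the equation value or a cart value, and use the same term in section 8.c(iii).
2. Compare each equation value with the oxygen uptake measured on the cart at the last completed stage. Because the test is submaximal, that uptake is a lower bound for VO2peak, so flag as invalid any prediction below it.
3. Report the level-based fitness analyses with and without flagged values, applying the rule identically in both arms and at all visits.
4. Do not substitute the submaximal uptake for VO2peak in the main analysis. Replacing only the low predictions would mix two quantities in one direction. Setting them missing in the main analysis would make missingness depend on fitness, possibly differently by arm after the intervention.

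Sections 5.b (Exercise groups and programmes), 5.d.VIII and 7.a must be reconciled on what is used when the equation gives no usable value. The 15 W start in the text and the 25 W first load in the table of section 5.d.VIII must also be reconciled.

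The cost is a short derivation rule, some flagged values and one sensitivity analysis. It needs no new data if the cart readings are kept by stage.
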